### Exposure variables

–Number of days with propofol therapy preceding transition day from one clinical state to another (numeric variable), irrespective of whether a patient had propofol on transition day or not (for definition of state transitions see Figure 1)–The cumulated amount of propofol-associated energy intake (kcal/kg) (numeric variable) preceding transition day, irrespective of whether a patient had propofol on transition day or not–The amount of daily propofol-associated energy intake (kcal/kg and day) on transition day (numeric variable)–The amount of daily propofol-associated energy intake (kcal/kg and day) (categorized variable) during different phases after ICU admission. The associations of daily propofol-associated energy intake with the outcome will be cumulated for the early phase (Days 0 - 4 after ICU admission) and the late phase (Days 5 - 11 after ICU admission).

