### Confounder variables

The list of confounder variables is presented in table 1. To account for heterogeneity across ICUs, all models will include random effects for each unit.

**Table 1 t1:** List of confounder variables. In addition to these variables, all models will contain a random intensive care unit variable

Variable	Time of recording
Number of days on oral nutrition	Days 0 - 2 post ICU admission
Number of days on parenteral nutrition	Days 0 - 2 post ICU admission
Number of days with protein intake > 1.2g/kg day	Days 0 - 2 post ICU admission
Year of therapy	Admission date
APACHE II score	ICU admission
Main admission diagnosis*	ICU admission
Admission category (surgical elective/emergency, medical)	ICU admission
Age	ICU admission
Sex	ICU admission
BMI	Pre-ICU admission
Baseline number of days under MV†	Days 0 - 2 post ICU admission
Number of days under MV before state transition‡	Days 0 - 11 post ICU admission

ICU – intensive care unit; APACHE - Acute Physiology and Chronic Health Evaluation; BMI - body mass index; MV - mechanical ventilation.

* Gastrointestinal, cardio-vascular, metabolic, neurologic, orthopedic/ trauma, renal, pulmonary, sepsis, other. Sepsis was the main admission diagnosis, if there was an infection-associated circulatory dysfunction requiring vasopressor therapy which dominated dysfunction of other organs;

† only used when analyzing the association of daily propofol-associated energy intake (categorized variable) with time-to-discharge alive/in-hospital death (cumulated for the early and late phase after intensive care unit admission);

‡ only used in multistate models

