### Outcome measures

–**Primary outcomes:** time-to-hospital discharge-alive as a surrogate of morbidity, and to in-hospital death (adjusted hazard ratios and 95% confidence intervals [95%CI]).Adjusted hazard ratios compare two levels of daily propofol-associated energy intake. They will be calculated separately for each day after ICU admission using sub-distributional and cause-specific hazard models. The observation period will start on the day of ICU admission, and events (day of discharge alive/in-hospital death) will be registered from day 2 after ICU admission until the end of the lead-time (defined as twice the number of days that a patient received propofol therapy).–**Secondary outcomes:** the risk of state transition (adjusted hazard ratio and 95%CI) and the transition probabilities between the different states (Figure 1).State transition risks and probabilities will be referred to a certain amount of propofol-associated energy intake or a specific duration of propofol therapy; adjusted hazard ratios will be calculated for all 17 transitions (Figure 1). State transition will be registered until day 13 after ICU admission. Initial and absorbing states include "propofol: no/MV: no", "propofol: yes/MV: no", "propofol: no/MV: yes", "propofol: yes/MV: yes", post-transition absorbing states include "in-ICU death" and "ICU discharge alive.

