Hazard ratios can be used to describe the association of covariates and exposures with each transition (e.g., from alive to death in the ICU). In multistate settings, separate hazards are estimated for each possible transition. These individual transition hazards are then combined to obtain the overall transition probabilities by calculating the empirical transition matrix. While hazard ratios describe the direct effect on the instantaneous risk of a transition (relative risk), transition probabilities depend on the hazards of all possible transitions (absolute risk). Together, these two quantities provide a comprehensive interpretation of the underlying processes.

A particular focus will be on the concomitant use of MV, which is one of the main reasons for propofol use in critically ill patients and therefore the most important confounder of propofol-associated outcomes. The time-dependent confounder MV is considered as a separate state^(27)^ in the multistate model (Figure 1). This has the advantage that the transitions to the absorbing states "ICU discharge alive" and "in-ICU-death", and thus the transition probabilities to these states, can be modelled separately, depending on the current time-dependent propofol status (yes or no), but also on the subject-specific history of MV treatment and propofol administration (number of days with propofol therapy, cumulated propofol-associated energy intake). As the model is conditional on propofol status at any given time, but the frequency of MV use may vary between subjects within each propofol state, it allows the association of propofol and MV status with outcomes to be disentangled.

Results for the association between the exposure variables preceding transition (number of days with propofol therapy, cumulated propofol-associated energy intake (kcal/kg), propofol-associated energy intake (kcal/kg day) on transition day), and transition risk will be presented as adjusted hazard ratios (with 95%CIs) and adjusted transition probabilities (with 95%CIs) depending on a specific day after ICU admission (Days 1 to 11).

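### Multi-day transition probabilities tied to one propofol duration or cumulated intake need an attainable history that is updated along the state path

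*Protocol article*

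**What the plan says.** All of this comes from the protocol article.

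- **Estimator** (Overall design of the multistate models): "These individual transition hazards are then combined to obtain the overall transition probabilities by calculating the empirical transition matrix". The same paragraph presents hazard ratios as the relative-risk quantity and transition probabilities as the absolute-risk quantity.
- **Value at which they are reported** (Outcome measures, secondary outcomes): "State transition risks and probabilities will be referred to a certain amount of propofol-associated energy intake or a specific duration of propofol therapy".
- **Exposures** (Exposure variables): "Number of days with propofol therapy preceding transition day from one clinical state to another (numeric variable"; "The cumulated amount of propofol-associated energy intake (kcal/kg) (numeric variable) preceding transition day"; and, separately, the daily intake on the transition day itself.
- **Ventilation history** (Table 1, multistate models only): "Number of days under MV before state transition".
- **State space** (Outcome measures): four transient states crossing propofol yes/no with ventilation yes/no, plus in-ICU death and ICU discharge alive.
- **History dependence** (Overall design of the multistate models): transitions to death and discharge depend on current propofol status, "but also on the subject-specific history of MV treatment and propofol administration (number of days with propofol therapy, cumulated propofol-associated energy intake".
- **Reporting**: adjusted hazard ratios and transition probabilities are shown by day after ICU admission, days 1 to 11.

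The article does not say how propofol days, cumulated intake or ventilation days advance when hazards are combined over more than one day. Nor does it say that they are held constant.

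**The concern.** The empirical transition matrix is a product over time of one-interval matrices. Such a product can be evaluated at a fixed covariate value when the covariate is a baseline characteristic or is set from outside the process. Here the covariates are generated by the process being modelled. Propofol yes/no is part of the state, so prior propofol days is simply the number of earlier days spent in propofol-yes states. Prior ventilation days is the same kind of count for ventilation. Cumulated intake is not a count of days, but it can grow only on propofol-yes days.

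A product over several days at, say, 7 prior propofol days therefore has two faults. It uses the 7-day hazard on days by which no patient can have accumulated 7 days. It also moves patients in and out of propofol while leaving the count at 7. For any path that includes a propofol day, the resulting number matches no coherent patient history.

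These probabilities are a named secondary outcome and the absolute-risk half of the multistate results, in a study whose general aim is evidence on safe dosing and duration. Readers will take a probability labelled with a duration as the risk of a patient with that duration.

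**Working it through.** The article gives no figure for this point, so there is nothing to reproduce. Two checks were made.

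**1. Attainable combinations.** Days run from 0 (admission) to 11. Prior propofol days on day d are counted over days 0 to d − 1, so the count D cannot exceed d.

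- Grid of days 1 to 11 by D = 0 to 11: 11 × 12 = 132 cells.
- Attainable cells: sum over d = 1 to 11 of (d + 1) = 66 + 11 = 77, or 58%. The other 55 are impossible (45 if the transition day is also counted).
- In a product of 12 daily steps from day 0 to day 12, D = 7 is impossible on the steps starting on days 0 to 6 (7 of 12), and D = 10 on those starting on days 0 to 9 (10 of 12).

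**2. Fixed against updated history.** The documents give no transition hazards, so all hazards below are assumed and serve only to show direction. The one-day matrix is P(D) = exp(Q(D)), where Q(D) holds the daily hazards at count D.

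- *Fixed*: starting state × P(D) × P(D) × …, with D constant.
- *Updated*: the same product, with D raised by 1 after each day that starts in a propofol-yes state.

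*Model A*: states on propofol, off propofol, ICU death, discharge. Daily hazards: on to off 0.20; off to on 0.05; death 0.02 on and 0.01 off; discharge 0.02 on and 0.12 off. The death hazard is multiplied by HR^D. Patients start on propofol.

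| Probability of ICU death | HR 1.05 per prior day | HR 1.10 per prior day |
|---|---|---|
| Day 0 to 12, D fixed at 7 | 16.9% | 22.4% |
| Day 0 to 12, D fixed at 10 | 19.2% | 28.4% |
| Day 0 to 12, D updated from 0 | 14.4% | 16.9% |
| Day 7 to 12, D fixed at 7 | 10.1% | 13.7% |
| Day 7 to 12, D updated from 7 | 10.9% | 15.9% |

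The rows must be compared over the same period: the first three cover 12 days, the last two cover five.

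*Model B*: the article's four transient and two absorbing states, with other assumed hazards. All 4 × 5 = 20 transitions are allowed, rather than the 17 of Figure 1. The death hazard is multiplied, and the discharge hazard divided, by HR^D. Patients start on propofol and ventilated.

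| Probability of ICU death | HR 1.05 | HR 1.10 | HR 1.20 |
|---|---|---|---|
| Day 0 to 12, D fixed at 0 | 0.167 | 0.167 | 0.167 |
| Day 0 to 12, D fixed at 5 | 0.215 | 0.269 | 0.395 |
| Day 0 to 12, D fixed at 10 | 0.272 | 0.408 | 0.721 |
| Day 0 to 12, D updated from 0 | 0.195 | 0.228 | 0.307 |
| Day 5 to 12, D fixed at 5 | 0.154 | 0.192 | 0.285 |
| Day 5 to 12, D updated from 5 | 0.170 | 0.234 | 0.403 |
| Day 5 to 6, D = 5, either method | 0.026 | 0.032 | 0.050 |

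Three things follow when the assumed association is harmful:

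- From day 0, fixing D at a high value overstates the risk, and fixing it at 0 understates it.
- From an attainable landmark, fixing D understates the risk, because the count would have gone on rising.
- One-day probabilities agree exactly, and at HR 1.00 the two methods agree throughout.

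**The case against.** The strongest reply is that the article never says the exposure is held fixed through a multi-day product. That is inferred from the estimator in one section and the reporting value in another. Results are to be shown by day, exposures are defined relative to the transition day, and the piecewise exponential model was chosen partly because it handles time-dependent covariates. All of this is compatible with one-day probabilities given the history so far, and those are valid. The article also sends the reader to its references for details, and a condensed article may leave the prediction step to a fuller plan.

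Much of this stands. The fault is conditional on the multi-day reading, and the one-day reading cannot be excluded. It does not dispose of the point. Overall probabilities from an empirical transition matrix fit a multi-day product better than a single step. The article fixes both an estimator and a conditioning value, and for multi-day probabilities the two do not fit together. For the primary analysis, by contrast, it lays out daily exposure histories, time windows and hypothetical intake patterns. Even one-day results need the duration not to exceed the elapsed days.

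Two stronger readings are tempting and are not supported. A reader might infer that every such probability describes an impossible history. That goes too far: a path that stays off propofol keeps its propofol days and cumulated intake constant, cumulated intake depends on daily amounts as well as on days, and intake on the transition day is not accumulated at all. A reader might also infer that associations with duration or dose are always exaggerated on the absolute scale. The calculations contradict this, because the direction depends on the start day and on the value chosen.

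**Conclusion.** The point holds in conditional form. If the transition probabilities are multi-day products at one fixed duration or cumulated intake, they are not the risks of patients with that history, and the error can go in either direction. This goes beyond missing detail, because applying the stated estimator at the stated value over several days gives an incoherent absolute risk for a named secondary outcome.

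The count of 77 attainable cells out of 132 rests only on the article's day scale and exposure definition. The risk differences (for example 22.4% against 16.9% from day 0, and 13.7% against 15.9% from day 7, in Model A at HR 1.10) rest on assumed hazards and say nothing about the size to expect in this database.

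The scope is limited. The transition hazard ratios, the primary outcome and one-day probabilities at an attainable history are not touched. The change is worth making before the analysis is run; it does not undermine the study.

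**What to change.** In Outcome measures and in Overall design of the multistate models:

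1. State whether the transition probabilities are one-day or multi-day.
2. Define each probability from a landmark day, a current state and an attainable history: prior propofol days no greater than the elapsed days, with matching cumulated intake and prior ventilation days.
3. Report either the one-day probability from that point, or the probability to day 12 with propofol days, cumulated intake and ventilation days updated daily along each path. This can be done by simulating from the fitted models or by extending the state space with the counts. Intervals can come from drawing model coefficients.
4. Do not multiply daily matrices at a fixed duration or cumulated intake.
5. Limit day-specific displays, including those of hazard ratios, to attainable combinations of day and prior propofol days.

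The cost is analysis programming, plus a stated assumption about daily intake on future propofol days if cumulated intake is simulated. No new data are needed.

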## INTRODUCTION

Recently, controversy has arisen regarding whether propofol has undesirable side effects compared to other sedative drugs.^(1)^ These effects may mainly occur in patients over 65 years of age,^(2)^ but have also been observed in pediatric populations.^(3)^ A meta-analysis by Kotani et al.^(1)^ involving 252 randomized controlled trials and more than 30,000 patients found that the use of propofol is associated with a potential 10% increase in mortality compared with other sedation strategies. This fatal side effect may also be relevant for critically ill patients, for whom there was a 10% relative increase in mortality (15% *versus* 13%), with a Bayesian approach indicating a 75.7% probability of harm.^(4)^

In contrast, other meta-analyses have found that, compared to midazolam, the use of propofol does not worsen the outcome for a heterogeneous population of critically ill adult patients,^(5)^ and may even reduce the length of stay in the intensive care unit (ICU), the duration of mechanical ventilation (MV) and the time to extubation for acutely ill surgical patients.^(6)^ Two recent meta-analyses compared propofol with dexmedetomidine. On the one hand, there was no difference in mortality.^(7,8)^ However, in the meta-analysis by Heybati et al.,^(7)^ for example, mortality was only an endpoint in four trials involving 364 patients. This small sample size may have contributed to the very low certainty of these negative results. Conversely, Heybati et al.^(7)^ found that propofol may increase the duration of MV and lengthen hospital stays for unselected patients, as well as increasing the risk of ICU-associated *delirium* in cardiac surgery patients.

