### Limitations

This study is subject to the inherent limitations of observational studies, including selection bias, information bias, confounding due to informative missing data (e.g., malignant diseases), confounding by indication, and residual confounding due to unmeasured variables. In terms of propofol use, confounding by indication is highly relevant. The main confounding factor is the concurrent use of MV, which indicates underlying respiratory dysfunction. This could lead to an erroneous association between propofol use and a worse outcome, when in fact the worse outcome is caused by the respiratory dysfunction. To minimize this bias, all models will adjust for the concomitant duration of MV in propofol-related associations. Another confounding factor is the use and dosing of propofol in end-of-life care. To minimize this bias, sensitivity analyses will be performed that exclude suspicious state transitions and events occurring close to the last day of propofol therapy (lag time).

Due to the characteristics of our database, we do not have information on concomitant central nervous system dysfunction (e.g., septic *delirium*) in the absence of MV use. This type of organ dysfunction may also require propofol administration and may also be associated with a worse outcome. We have attempted to account for at least some of this bias by adjusting propofol-related associations with the outcome for baseline APACHE II scores (which contain information on the Glasgow Coma Score) and the sepsis admission diagnosis.

Another limitation is that we will be unable to analyze state transitions (multistate models) occurring within 24 hours due to missing information. Furthermore, as propofol data collection ended on day 11 after ICU admission, transition hazards can only be evaluated up to this point, and associations of propofol use with outcomes can only refer to this therapeutic period. However, as recent randomized studies (e.g., SPACE III) only recorded interventional sedation for a median of 2.6 days (IQR 1.10 - 5.3 days),^(30)^ we believe that the maximum therapeutic period (up to day 11 after ICU admission) should provide sufficient time to draw meaningful conclusions about propofol use.

Patients had not been followed after hospital discharge. Therefore, hospital discharge is treated as an endpoint, with in-hospital death as a competing event, and is accounted for using competing risks modeling (cause-specific and Fine and Gray approaches).

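### The multistate death and discharge hazard ratios are conditional on a ventilation history that propofol may itself change, so alone they cannot support a safety statement

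*Protocol article*

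**What the plan says.** The section Overall design of the multistate models gives MV one role. It is described as a factor "which is one of the main reasons for propofol use in critically ill patients and therefore the most important confounder of propofol-associated outcomes". It enters the model in two ways:

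- **As part of the current state:** "The time-dependent confounder MV is considered as a separate state".
- **As a running count:** Table 1 (Confounder variables) lists "Number of days under MV before state transition", recorded over days 0-11, with a footnote that it is "only used in multistate models".

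The same section concludes that "it allows the association of propofol and MV status with outcomes to be disentangled". It describes hazard ratios as direct effects on a transition's instantaneous risk, and transition probabilities as absolute risks that depend on every transition hazard. Hazard ratios are planned for all 17 transitions (Outcome measures).

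The primary competing-risk models carry a different term, "Baseline number of days under MV", recorded on days 0-2 only. The Limitations section nevertheless says: "To minimize this bias, all models will adjust for the concomitant duration of MV in propofol-related associations".

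The Introduction cites one meta-analysis in which "propofol may increase the duration of MV and lengthen hospital stays for unselected patients", and another, against midazolam in acutely ill surgical patients, in which MV duration may be reduced.

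**The concern.** If propofol can change how long a patient stays ventilated, MV after the first propofol day is partly a consequence of propofol and not only a reason for giving it. A death hazard ratio taken within an MV state, at a given number of MV days, then differs from the overall association in two ways.

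- It leaves out whatever runs through ventilation: harm if propofol prolongs MV, benefit if it shortens MV.
- It compares unlike patients. If propofol prolongs MV, then among patients with the same MV history, those with more propofol needed less illness to remain ventilated. Where severity is not fully measured, as the Limitations section admits, this pushes the hazard ratio downwards.

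The stated general aim is evidence on safe dosing and duration. Duration of propofol therapy, part of the study's primary purpose in the Introduction, is an exposure only in the multistate models (Exposure variables; Table 2). A reader who took the death hazard ratios for duration or cumulated intake as the safety result could be misled.

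**Working it through.** **The plan's own figure.** The only sample-size figure reproduces: 18,000 × 0.70 = 12,600 discharges, consistent with more than 10,000. It has no bearing on this point.

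**Step 1: what happens to the death hazard ratio.** The documents give no parameters, so all of these are assumed. The simulation had 150,000 patients, all ventilated at the start, over 12 daily intervals. High or low propofol was assigned at random, so there was no confounding by indication.

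- Daily death hazard: 0.012, × 2 while ventilated, × 1.08 per prior MV day.
- Daily extubation hazard: 0.25, multiplied by 0.6 or 0.8 under high propofol.
- Daily discharge hazard once off MV: 0.20.
- Unmeasured severity: log-HR 0, 0.5 or 0.8 per SD on death, with the opposite sign on extubation.

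The fits were discrete-time piecewise models (complementary log-log link, day-specific baseline). Risk ratios (RR) are high versus low propofol, from unrounded risks.

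| Scenario | 12-day death risk, low / high | RR | Death HR, unadjusted | Death HR given MV state and MV days (95% CI) | HR, MV to no MV |
|---|---|---|---|---|---|
| Null | 0.1730 / 0.1708 | 0.99 | 0.99 | 0.99 (0.97-1.01) | 1.00 |
| Extubation 0.6, severity 0 | 0.1731 / 0.2139 | 1.24 | 1.13 | 0.98 (0.96-1.01) | 0.60 |
| Extubation 0.6, severity 0.5 | 0.2029 / 0.2425 | 1.19 | 1.09 | 0.93 (0.91-0.95) | 0.64 |
| Extubation 0.6, severity 0.8 | 0.2387 / 0.2757 | 1.16 | 1.06 | 0.90 (0.88-0.92) | 0.67 |
| Extubation 0.8, severity 0.8 | 0.2391 / 0.2547 | 1.07 | 1.03 | 0.95 (0.93-0.97) | 0.85 |
| Extubation 0.6, severity 0.8, true direct death HR 1.10 | 0.2378 / 0.2947 | 1.24 | 1.16 | 1.00 (0.98-1.02) | 0.68 |

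Without unmeasured severity the harm through MV drops out and the hazard ratio sits near 1. With it, the hazard ratio falls below 1, and in the last row it hides a genuine direct effect. Fits within each state agree: in the three severity scenarios without a direct effect, the death HR was 0.90 to 0.96 while ventilated and 0.89 to 0.93 when not. The delayed extubation stays visible in the last column.

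**Step 2: what the transition probabilities keep.** Here propofol had no direct effect on death and raised the odds of staying ventilated the next day. MV acted on death through current state (log-HR 0.6). The contrast was propofol on all versus no ventilated days. Probabilities were computed from fitted state-specific hazards with MV days held at each day's mean.

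| Odds ratio for staying ventilated, severity log-HR | True risk ratio | From probabilities, MV days fixed |
|---|---|---|
| 1.5, 0.7 | 1.08 | 1.07 |
| 2.0, 0.4 | 1.14 | 1.11 |
| 2.0, 0.7 | 1.13 | 1.13 |

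A further set of runs, also with assumed parameters and no direct effect, gave:

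- True ratios of 1.07 to 1.17, with death hazard ratios of 0.83 to 0.97 in the three well-populated states.
- Hazards run forward with MV responding: 1.05 to 1.19.
- MV days held fixed: 1.03 to 1.14. The loss was clear only when MV days had its own effect on death: 1.16 fell to 1.12 and 1.17 to 1.11, that is 0.04/0.16 = 25% and 0.06/0.17 = 35% of the excess.

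**Step 3: the primary models.** By the Table 1 footnotes, time-updated MV days does not enter them. They adjust for MV days 0-2, while intake is modelled to day 11. Days 0-2 overlap exposure from day 0, so they are not wholly free of the problem, but an effect through MV after day 2 is not adjusted away. This does not match the Limitations statement that every model adjusts for concomitant MV duration.

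**The case against.** The strongest reply is that the plan does not rest on the death hazard ratios alone. It models MV as a state, reports hazard ratios for all 17 transitions, and pairs them with transition probabilities as the absolute-risk quantity. Step 2 bears this out: the pathway through MV state mostly reappears in those probabilities, even with MV days held fixed. The multistate outcomes are also secondary. The primary models already contrast hypothetical propofol patterns and leave effects through later ventilation largely intact. All of this stands.

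It does not remove the point. The death and discharge hazard ratios will still be reported, and the disentangling claim is attached to the model that yields them. Calling them direct effects contrasts a single transition with absolute risk; it is not a caveat about mediation, and with unmeasured common causes of MV and death they are not clean direct effects either. Nor does the text say how MV days is carried forward in the probabilities. A full plan may say so, and that silence alone would be no fault.

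A reader might infer more than the documents support:

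- **That harm through ventilation vanishes from the study.** It remains in the MV-transition hazard ratios, mostly in the transition probabilities, and largely in the primary analysis.
- **That the plan freezes MV days.** Nothing says so; the design section calls prior MV days a time-dependent covariate.
- **That the net result will be false reassurance.** The simulations exclude confounding by indication, which the Limitations section calls highly relevant and which can bias towards harm. The cited evidence on MV is also hedged and runs both ways.
- **That MV should be dropped.** It is a real confounder.

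**Conclusion.** The point holds for the multistate hazard ratios for death and discharge, and for the wording of two claims. By the protocol's own cited evidence, MV after propofol starts may be a mediator. Conditioning on it leaves out effects through ventilation and, with unmeasured severity, can push the death hazard ratio below 1 when propofol prolongs MV.

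Under the Step 1 assumptions, and with no direct effect, risk ratios of 1.07 to 1.24 went with adjusted hazard ratios of 0.98 (no unmeasured severity) and 0.90 to 0.95 (with it). These sizes are illustrative, and a risk ratio is not on the same scale as a hazard ratio; only the direction is general. Apparent protection needs an unmeasured common cause of prolonged MV and death.

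The transition probabilities lose a material part only if MV days is held fixed and itself affects death. The primary analysis is much less affected. This is a worthwhile, inexpensive improvement to a secondary analysis, not a fault in the primary one.

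**What to change.** 1. Keep MV in the multistate models, and name it as both confounder and possible mediator.
2. Describe the MV-conditional death and discharge hazard ratios as associations at fixed ventilation history that do not by themselves support a safety statement.
3. For the multistate part, base dose and duration conclusions on the planned transition probabilities to day 12 under contrasting propofol patterns. Compute them by running the fitted hazards forward with MV state, MV days and propofol history updated along the path. Give 95% CIs that respect clustering by ICU, for example a bootstrap that resamples ICUs.
4. Amend the disentangling sentence in Overall design of the multistate models to match.
5. In Limitations, reconcile the sentence on MV adjustment with Table 1: time-updated MV days in the multistate models, MV days 0-2 only in the competing-risk models. Add that adjusting for later MV may also remove part of propofol's own association with outcome.

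The cost is changed wording and one simulation step on models already planned, with no new data. The downsides are more computing and a risk contrast in place of a single hazard ratio. Residual confounding by indication remains.
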